#### Analysis of Trial Outcome Data

##### Primary Outcomes

Changes in outcomes across pre-, post-, and follow-up assessments (PTQ, EBQ, PBRS, NBRS, HADS, CAQ, and BEAQ) will be analyzed using mixed-design ANOVA across all 4 conditions. Additionally, multilevel models—treating daily observations as level 1 and participants as level 2—will be used to assess associations between avoidance and mood, as well as between rumination and mood, and to examine whether these associations are moderated by condition.

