**Methods:**

Consenting individuals (target N=60) who meet the inclusion criteria (self-reporting problems with repetitive negative thinking) will be randomly assigned to 1 of 4 conditions: (1) intervention with therapist support and daily sampling, (2) intervention without support and with daily sampling, (3) partial intervention (emotion validation EMI only) with daily sampling, or (4) control (daily sampling only). The intervention consists of a series of modules delivered over 4 weeks, with assessments conducted before and after intervention, and again at 1-month follow-up (plus an additional 3-month follow-up for intervention participants). Data will be collected both through online self-report assessments and via the app itself. The potential of the EMI to modify the maladaptive feature of repetitive negative thinking will be assessed using mixed-design ANOVA, while the links between avoidance-mood and rumination-mood, in terms of the moderating effect of trial condition, will be evaluated using multilevel models. These will be assessed as primary outcomes. Secondary outcomes are the effects of a supporting therapist on postintervention outcomes in the intervention groups, and time spent using the app as a measure of engagement (analyzed using the mixed-design analysis of covariance). Compliance will be defined as completing both of the first 2 weeks of intervention content in full, and 5 out of the 6 exercises from weeks 3 and 4. Additionally, the study will control for both the amount of time spent in the app and the length of responses to open-ended questions.

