### Study Objectives

The scientific verification of processes that underpin several transdiagnostic maladaptive cognitive processes and psychopathological outcomes has several benefits. First, successfully identifying such processes advances the theoretical understanding of transdiagnostic processes themselves and their contributing roles in psychopathology. Second, it has the potential to improve several psychological treatment programs by identifying valuable targets for intervention [21], which is particularly valuable in treating cases of comorbidity. Using EMI and EMA in clinical trials offers a unique opportunity to evaluate the mechanisms underlying transdiagnostic processes that are difficult to assess through traditional self-report or laboratory methods (eg, avoidance). This study aims to examine whether the avoidance-focused EMI for rumination can modify the maladaptive feature of RNT, as understood through the link between daily RNT and well-being, depressive, and anxiety symptoms, compared with an active control group. We anticipate that the link between daily rumination and its maladaptive outcomes (lower well-being and higher depressive and anxiety symptoms) will be weaker in the intervention groups compared with the control group. Additionally, the study aims to confirm the role of avoidance in RNT.

Furthermore, by splitting the intervention condition into 2 groups (1 receiving concurrent therapist support and 1 not receiving concurrent therapist support), the study aims to evaluate whether intervention outcomes may be enhanced by the added availability of a supporting therapist [61].

Finally, the study aims to examine whether the impact of the avoidance-focused EMI for rumination on depressive and anxious symptoms can, compared with an active control group, be mediated by changes in beliefs about emotion (valuation of negative emotions) [62]. Similarly, the study aims to assess the EMI in terms of similar mediation effects of beliefs about rumination [63].

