### Participants and Power Analysis

Participants who self-report problems with RNT will be sought. The first participation in the trial is planned to commence in May 2025. As the study will be conducted remotely and recruitment will continue beyond this date, participants are expected to begin their engagement asynchronously.

To be eligible for the trial, participants must self-report problems with RNT. Participants will be excluded if (1) they are under 18 years of age at the start of the trial; (2) they are currently receiving any form of psychotherapy; or (3) they are currently receiving any form of psychiatric medication. Participants with a psychiatric diagnosis will not be excluded, provided they meet the inclusion criterion and do not meet any of the exclusion criteria listed above.

Sample size was calculated using G*Power version 3.1 [65] for a repeated-measures design with 4 independent conditions measured at 3 time points and assuming a medium effect size. This indicated a required sample size of 60 with equal randomization of participants across groups, which aligns with previous intervention studies in the field [66-68]. As our initial feasibility study during the development of the app content experienced an attrition rate of approximately 60% [69], this study aims to recruit at least double that number to mitigate the risk of significant dropout throughout the trial.

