### Measures

#### Pre-Post and Follow-Up Measures

The following measures will be collected from all participants before/during the intervention, after the intervention, and at follow-up:

The Perseverative Thinking Questionnaire (PTQ) [70], a 15-item self-report measure that assesses the main characteristics of RNT: (1) core features (9 items); (2) unproductiveness (3 items); and (3) capturing mental capacity (3 items). Responses are recorded on a scale from 0 (never) to 4 (almost always). The PTQ has demonstrated good internal consistency and test-retest reliability [70], not only in clinical samples, but also in nonclinical populations and when administered online.

Emotions Beliefs Questionnaire (EBQ), a 16-item self-report questionnaire designed to measure the controllability of emotions and respondents’ beliefs about the usefulness of emotions, which also demonstrates good internal consistency [71]. Respondents answer using a 7-point Likert scale, ranging from “1” (totally disagree) to “7” (totally agree), with higher scores indicating a belief that emotions are uncontrollable or useless.

The Positive and Negative Beliefs About Rumination Scales (PBRS and NBRS, respectively), which comprise 2 scales (positive beliefs: 9 items; negative beliefs: 13 items) that measure metacognitive beliefs related to depressive rumination. Respondents rate the extent to which they agree with each item using a 4-point Likert-type scale, ranging from “1” (do not agree) to “4” (agree very much), with higher scores on each subscale indicating greater positive or negative beliefs, respectively. Both the PBRS and NBRS demonstrate adequate to good internal consistency [72].

Hospital Anxiety and Depression Scale (HADS), a measure of the possible and probable presence of anxiety disorders and depression, comprising 7 items, developed by Zigmond and Snaith [73]. It has been shown to possess good internal consistency, with sensitivity and specificity comparable to the General Health Questionnaire [74]. Respondents rate each item on a scale of 0-3, with higher total scores for each subdomain (anxiety and depression) indicating a greater presence of the disorder. Thresholds for determining the clinical presence of the disorder are as follows: 0-7=normal, 8-10=borderline abnormal (borderline case), and 11-21=abnormal (case).

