## Discussion

### Study Strengths and Challenges

This paper outlines the protocol for a randomized controlled trial of an mHealth EMI aimed at reducing EA in the context of rumination. The primary objective of the trial is to investigate whether a reduction in EA through EMI intervention can lead to a decrease in RNT and its maladaptive consequences. Additionally, by implementing the CORTO method, the trial will gather user data on app usability and acceptability, identifying areas for continuous improvement and development.

While the primary objective of this study is to examine the role of EA, we are also collecting data on the use of the app itself. This information will inform its further development and potential efficacy testing in various settings. The app, as it currently stands, and its intervention content have been developed based on our formative user-experience research. While this approach is expected to enhance acceptability, usability, and user retention, and despite the app being thoroughly tested for issues, potential challenges during deployment to real-world users cannot be ruled out. For example, the app currently does not time-lock intervention modules and instead allows users to progress to the next week’s content once the preceding week’s material has been successfully completed. While this approach provides users with flexibility in how they complete the intervention, as recommended by prior studies [92,93], there is a possibility that some users may progress through the content more quickly than intended. This could potentially lead to poor information retention and a diminished impact of the intervention.

Definitions and reporting of compliance can vary significantly across studies of digital interventions [46]. The design of our app enables the remote collection of both daily assessment data and app usage metrics, allowing for precise measurement of engagement and, consequently, intervention compliance. For this study, we have adopted a compliance rate of 80%, consistent with a previous study using EMI and daily assessments with adult populations [89].

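### Seven questionnaires and two sets of daily-data models are all designated primary and none is singled out; one primary test, or a prespecified testing rule, is needed

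*Protocol article*

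**What the plan says.** The Primary Outcomes section of the protocol article names seven instruments: "PTQ, EBQ, PBRS, NBRS, HADS, CAQ, and BEAQ) will be analyzed using mixed-design ANOVA across all 4 conditions". It then adds multilevel models that "will be used to assess associations between avoidance and mood, as well as between rumination and mood", with a test of whether condition moderates each association. The Abstract (Methods) describes the same two strands and says of them: "These will be assessed as primary outcomes". Its secondary outcomes are therapist support and time in the app, so every pre-post outcome questionnaire is on the primary side.

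The HADS gives two scores, since the Measures section refers to "higher total scores for each subdomain (anxiety and depression" as separate totals. The seven instruments therefore yield at least eight scores.

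The purpose of the trial is described in two places with different emphasis:
- Study Objectives expects the link between daily rumination and its outcomes ("lower well-being and higher depressive and anxiety symptoms") to be weaker in the intervention groups. It also says that the effect on symptoms may "be mediated by changes in beliefs about emotion (valuation of negative emotions"), and it gives beliefs about rumination the same role.
- Study Strengths and Challenges says: "The primary objective of the trial is to investigate whether a reduction in EA through EMI intervention can lead to a decrease in RNT". The sentence goes on to include the harmful consequences of that thinking.

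The sample size of 60 was calculated "for a repeated-measures design with 4 independent conditions measured at 3 time points and assuming a medium effect size".

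**The concern.** A primary outcome tells the reader in advance which result decides the trial. Here the label covers everything measured before and after the intervention as well as the daily-data models, so it does not do that job. A favourable result on any one scale, or on either daily association, could be reported as a positive primary finding. With several chances to succeed, the probability of at least one such finding under no effect is well above the level used for each test.

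The statements of aim do not settle the choice. Study Objectives points to a moderation test on daily data. The Discussion could be served by the PTQ, the BEAQ or a daily model. The power section points to a four-group, three-occasion repeated-measures test without naming a scale.

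**Working it through.** **Inputs.** Seven questionnaires and two sets of multilevel models (Primary Outcomes); two HADS scores (Measures); 4 groups, 3 time points, N = 60, medium effect (Participants and Power Analysis). Assumed because the article does not state them: alpha 0.05 per test, f = 0.25 as the conventional medium effect, correlation 0.5 between time points, sphericity.

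**1. The plan's own figure.** For the group-by-time interaction, with k = 4 groups and m = 3 occasions:
- noncentrality = f² × N × m / (1 − rho) = 0.0625 × 60 × 3 / 0.5 = 22.5
- df1 = (k − 1)(m − 1) = 6
- df2 = (N − k)(m − 1) = 112
- power at alpha 0.05 = 95.4%

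N = 60 is the smallest equal-arm size that reaches 95%, so the stated figure is reproduced for one interaction test at 0.05 if 95% power was intended.

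**2. Chance of at least one false-positive primary, independent tests.** The formula is 1 − 0.95^n.

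| Tests counted | n | Chance |
|---|---|---|
| Seven questionnaires | 7 | 30.2% |
| Eight scores (HADS split) | 8 | 33.7% |
| Seven questionnaires + two model sets | 9 | 37.0% |

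**3. The same with correlated tests.** Self-report scales of related constructs will correlate. Nine tests were simulated with a common correlation, all nulls true. The 6-df version uses interaction F tests at N = 60; the 1-df version uses two-sided z tests.

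| Correlation | 6-df tests | 1-df tests |
|---|---|---|
| 0.3 | about 33-34% | about 32% |
| 0.5 | about 28-29% | about 27% |
| 0.7 | about 22-23% | about 20% |

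Across correlations of 0.3 to 0.7 the range is roughly 20-34%. At 0.9, with 6-df tests, it is still about 13-14%.

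**4. Price of keeping everything primary under Bonferroni-type control.** Same power formula, N = 60:
- alpha = 0.05/7 = 0.0071: power 82.5%
- alpha = 0.05/8 = 0.0063: power 81.3%
- alpha = 0.05/9 = 0.0056: power 80.2%

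To return to 95% would need N = 80 (seven tests) or N = 84 (nine tests). Holm is never less powerful than Bonferroni, so these power figures are lower bounds for Holm.

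**The case against.** The strongest reply is that this is a journal article and its analysis plan is not shown, so a multiplicity method may exist there. That stands. A reader might infer that the trial has no error control at all, and the article cannot support so much. The point rests on what the article itself fixes: it assigns primary status, and it assigns it to everything.

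A reader might also infer that the sample size ignored multiplicity. That is not established. Alpha, power and correlation are not stated, and N = 60 fits one test at 0.05 with 95% power and also 80% power at 0.05/7, 0.05/8 or 0.05/9 (N = 56 falls below 80% in each case). The stated N cannot tell these apart.

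Nor is it a contradiction that EBQ, PBRS and NBRS are both outcomes and proposed mediators. Testing whether condition changes a mediator is an ordinary step in a mediation analysis. Only the primary label on them is in question.

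The statements of aim are also not rival primary questions. Study Objectives never calls its aim primary and also mentions confirming the role of avoidance, and the Discussion sentence includes the consequences of repetitive negative thinking. They share a theme and differ in emphasis. What remains is that they do not point to one test.

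Finally, it is tempting to call a chance positive likely. It passes 50% only with a larger count, for example 8 scores plus 2 associations × 3 daily outcomes = 14 independent tests (51.2%). Study Objectives ties the three daily outcomes to rumination only, so extending them to avoidance is an assumption, and correlation pulls the figure down.

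**Conclusion.** The concern holds in this form: the Abstract and Primary Outcomes make seven questionnaires (eight scores) and two sets of moderation models primary without ranking them, and the stated aims do not supply the ranking. Choosing the primary endpoint belongs in the protocol, so a possible analysis plan does not remove the point.

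The size is a chance of about 30% (7 tests) to 37% (9 tests) of at least one false-positive primary result if tests are independent, and roughly 20-34% for 9 tests correlated 0.3 to 0.7, instead of 5%. This assumes 5% per test, no adjustment, no true effect, one test per questionnaire and per model set, and that success on any one outcome would count. It would not apply if success on all were required, but the article does not say so.

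The problem is moderate and cheaply corrected.

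**What to change.** In the Abstract and Primary Outcomes, designate one primary test that matches the stated aim and the sample-size design. Two candidates fit the article, and the choice is the sponsor's:
- **Condition-by-daily-rumination moderation**, which is the hypothesis in Study Objectives. One of the three daily outcomes, or a defined composite, must be named. The power section would need a justification for this model, because its calculation is for a different design.
- **PTQ condition-by-time interaction across the four arms**, which is the type of design in the power section.

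Make the other a key secondary, tested only if the first succeeds. List the remaining scales as secondary, with EBQ, PBRS and NBRS serving as mediators. Word Study Objectives and Study Strengths and Challenges to agree.

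If the sponsor prefers to keep all of them primary, prespecify Holm or a fixed testing order across them.

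The cost of the first route is mostly wording and the loss of primary status for the other scales. With Bonferroni-type control of 7 to 9 tests, power for one interaction test falls from about 95% to 80-82% at N = 60, under f = 0.25 and correlation 0.5. A fixed order avoids splitting alpha, but an early failure stops all later confirmatory tests. Either change should be dated and made before outcome data are examined.

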	**Module 3**			
		Exercise 3	Summarizing learning: identifying the context, content, consequences of users’ rumination, and how to reduce rumination and its maladaptive consequences.	

During the development process, an initial feasibility study was conducted to consult with prospective end users. Participatory workshops were held to obtain feedback on the usability and acceptability of the app content and to discuss preliminary plans for the app structure, visual layout, and features [69]. Before these workshops, participants, selected based on their rumination levels, were asked to engage with a web-based version of the proposed app content (hosted via Qualtrics; SAP SE) for 4 weeks. Participants were asked to complete a series of pre- and posttests online, designed to mimic the randomized controlled trial protocol for this trial (see the “Methods” section, except for the BEAQ measure). A series of attentional tests was also included in the online assessment to control for response reliability. To be included in the analysis, participants were required to complete the first 2 weeks of content in full, followed by 5 of the 6 exercises from weeks 3 and 4.

Of the initial 687 participants who registered interest in participating, a sample of 55 was selected through prescreening using the PTQ. Participants were selected if their overall score was 1 SD above average. Of these, 21 participants completed all measures and were included in the quantitative analysis. Four participants volunteered to engage in participatory workshops and took part in semistructured interviews with members of the research team. The semistructured interviews focused on (1) factors determining compliance and strategies to overcome challenges in following the 4-week program; (2) strong and weak aspects identified in the program content; (3) accessibility of psychoeducational content in terms of language, clarity, and length; (4) strong and weak aspects of the user experience; (5) evaluation of different exercise types; and (6) evaluation of a mock-up for apps, with users having previous experience following the 4-week program.

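### The mixed-design ANOVA of the questionnaires tests a 6-df group-by-time interaction, not intervention versus control, and in its classical form drops anyone who misses an assessment

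*Protocol article*

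**What the plan says.** All references are to the protocol article.

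- **Primary Outcomes** (under Statistical Analysis): changes in PTQ, EBQ, PBRS, NBRS, HADS, CAQ and BEAQ across the three assessments "will be analyzed using mixed-design ANOVA across all 4 conditions". No contrast between arms is named. The same section adds multilevel models of daily data, with moderation by condition, as a second primary analysis.
- **Study Objectives**: the aim is framed as the avoidance-focused intervention against an active control group. The directional prediction, that something "will be weaker in the intervention groups compared with the control group", refers to the link between daily rumination and its outcomes.
- **Participants and Power Analysis**: the calculation was for "4 independent conditions measured at 3 time points and assuming a medium effect size". The total it produced is reported in the next sentence: "This indicated a required sample size of 60 with equal randomization of participants across groups". Because the feasibility study "experienced an attrition rate of approximately 60" percent, "this study aims to recruit at least double that number".
- **Development, Content, and User Evaluations** (after Table 1): in the feasibility study "a sample of 55 was selected through prescreening using the PTQ". The article then reports how many finished: "Of these, 21 participants completed all measures and were included in the quantitative analysis".
- **Recruitment Strategy**: the data of anyone who withdraws are deleted.
- **Data Exclusion**: sets compliance thresholds and excludes participants who fail both attention checks.

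**The concern.** The named test and the question do not match. An interaction over four arms and three times can be significant because of any difference in trajectory, for example the partial arm differing from a full-intervention arm. It can also miss a real benefit in the intervention arms, because its power is spread over six dimensions. Without a named contrast, the comparison that carries the claim could be chosen after the results are seen.

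The second issue is incomplete follow-up. A classical mixed-design ANOVA uses only people with pre, post and 1-month scores. Someone who gives baseline and post scores but misses the last assessment contributes nothing. If dropout depends on earlier scores, the remaining complete cases can give a biased comparison.

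**Working it through.** **1. The plan's own figure.** Inputs from the article: 4 groups, 3 times, medium effect, N = 60. Alpha, power, correlation and nonsphericity are not given. I assume f = 0.25, alpha 0.05, rho 0.5 and epsilon 1. For the interaction:

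- df1 = (4-1)(3-1) = 6; df2 = 2(N-4) = 112
- lambda = f² × N × 3/(1-rho) = 0.0625 × 60 × 3/0.5 = 22.5
- power = 0.954

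Under these settings N = 60 is the answer for 95% power (80% power gives 40; 90% gives 52). So the stated size is consistent with the 6-df test being the planned one.

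**2. Number analysable.** Doubling 60 gives 120. At 60% loss, 120 × 0.4 = 48 complete cases, 12 per arm. The feasibility loss was 34/55 = 61.8%.

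**3. Power for the question asked.** Assume SD 1, rho 0.5, arms 1 and 2 better by d at post and at 1 month, and arm 3 equal to arm 4.

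- *6-df interaction.* The squared interaction effects sum to 2d²/3, so lambda = (N/4)(2d²/3)/(1-rho) = N·d²/3 at rho 0.5. At N = 48 this is 16d².
- *1-df contrast of arms 1+2 versus 4 within the ANOVA.* The outcome is the mean of post and 1 month, minus baseline. Its variance is (1+rho)/2 + 1 - 2rho = 0.75. The arms contribute 2/N + 4/N = 6/N, so lambda = d²/(0.75 × 6/48) = 10.67d².
- *Same contrast, baseline as covariate.* The variance is (1+rho)/2 - rho² = 0.5, so lambda = d²/(0.5 × 6/48) = 16d².

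| N, d | 6-df test | 1-df contrast in ANOVA | 1-df, baseline-adjusted |
|---|---|---|---|
| 48, 0.6 | lambda 5.76: 36% | 3.84: 48-49% | 5.76: 65% |
| 48, 0.75 | 9.0: 55% | 6.0: 67-68% | 9.0: 83% |
| 60, 0.75 | 11.25: 68% | 7.5: 77% | 11.25: 91% |

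Where a range is shown, it reflects N-4 or 2(N-4) error degrees of freedom. These powers sit below the plan's because lambda = 22.5 at N = 60 corresponds to 20d² = 22.5, or d = 1.06, under this pattern.

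**4. Sensitivity to rho (N = 48, d = 0.6).** The three lambdas are 2.88/(1-rho), 2.88/[1.5(1-rho)] and 2.88/[(1+rho)/2 - rho²].

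- rho 0.3: lambda 4.11, 2.74, 5.14; power about 26%, 37%, 60%.
- rho 0.7: lambda 9.6, 6.4, 8.0; power about 59%, 70%, 79%.

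The order does not change.

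**5. What a significant omnibus test can mean.** Suppose only arm 3 improves, by 0.6 SD, and arms 1, 2 and 4 are equal. The squared effects sum to (3/4)(2/3)d² = 0.5d², so lambda = 12 × 0.5 × 0.36/0.5 = 4.32. The 6-df test is then significant about 27% of the time although intervention and control do not differ.

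**6. Partial completers.** Steps 3 to 5 use the same people throughout, so they contain no gain from incomplete records. A separate simulation (2,000 runs, 120 randomised, 45% lost by post and 60% by follow-up at random, covariance known, arm 3 at d/2) gave the following at d = 0.5:

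- complete cases: 0.20 (6 df) and 0.36 (1 df)
- all available data: 0.28 (6 df) and 0.51 (1 df)

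The loss pattern is assumed, so these figures are illustrative.

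**The case against.** - **The article states no missing-data rule.** Imputation or planned contrasts could stand in an analysis plan that is not shown. This stands: a reader might infer that the plan states a complete-case analysis, and it does not. What supports that handling is indirect: the classical form of the named method, a sample size that treats 60 as the number to be left after dropout, and the feasibility precedent of analysing the 21 completers.
- **The directional sentence in Study Objectives is about the daily rumination-outcome link.** The multilevel models test that link, and they can keep partial daily records. This stands too, so the sentence cannot be used as a hypothesis about questionnaire scores. The broader framing against an active control group remains, and the ANOVA contains no test of it.
- **The 60% comes from a web-based feasibility version.** It is not a forecast for this app. Recruitment is also to continue until each condition reaches its target, so 48 is an illustration. At N = 60 and d = 0.75 the gap is still 68% versus 91%.
- **A contrast can be tested inside an ANOVA.** This is correct. At N = 48 and d = 0.6, naming it moves power from 36% to 48-49%; baseline adjustment supplies the rest. A reader might credit the whole rise to 65% to recovered dropouts, but none of it comes from them.
- **A mixed model cannot recover everything.** Withdrawn participants' data are destroyed, and others are excluded by rule. This stands and limits the gain to people who stop responding without formally withdrawing.

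**Conclusion.** The point holds as a should-fix. The ANOVA is a valid, conventional method, but its group-by-time test does not answer whether the intervention arms beat control, and this is so even with no dropout. In its classical form it would also discard partial completers, though that handling is implied and not written.

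Under the stated assumptions (rho 0.5, arm 3 equal to control, d = 0.6, 48 analysable), the cost is 36% power against 65%. The size of the gap varies with rho and with the pattern across arms. Any further gain from partial completers depends on how many give a post score without withdrawing, which the article does not tell us. The criticism does not extend to the daily multilevel models.

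**What to change.** Replace the mixed-design ANOVA for the questionnaires with a linear mixed model for the post and 1-month scores:

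- baseline score as covariate, arm-by-time terms and an unstructured covariance;
- every randomised participant with any retained post-baseline score included;
- intervention arms 1+2 versus arm 4 pre-specified as the primary 1-df contrast;
- arm 1 versus arm 2, and arms 1+2 versus arm 3, as secondary contrasts.

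State alongside it how the deletion of withdrawn participants' data and the exclusion rules define the analysed set.

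The cost is a change of analysis wording and a different standard procedure, with no new data or visits. There are two downsides. The model relies on data being missing at random, which is weaker than what complete-case ANOVA generally needs but is still an assumption. And a single primary contrast gives up power for other patterns, such as an effect in arm 3 only.
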